## Abstract

The aim of the present study is to examine the acute effects of a specially designed musicokinetic (MSK) program for patients with Parkinson’s disease (PD) on (a) anxiety levels, (b) select kinematic and kinetic parameters, and (c) frontal cortex hemodynamic responses, during gait initiation and steady-state walking. *Methods*: This is a blind cross-over randomized control trial (RCT) in which 13 volunteers with PD will attend a 45 min MSK program under the following conditions: (a) a synchronous learning format and (b) an asynchronous remote video-based format. Changes in gait biomechanics and frontal cortex hemodynamic responses will be examined using a 10-camera 3D motion analysis (Vicon T-series, Oxford, UK), and a functional near-infrared spectroscopy (f-NIRS-Portalite, Artinis NL) system, respectively, while anxiety levels will be evaluated using the Hamilton Anxiety Rating Scale. *Expected results*: Guided by the rules of music, where periodicity is distinct, our specially designed MSK program may eventually be beneficial in improving motor difficulties and, hence, reducing anxiety. The combined implementation of f-NIRS in parallel with 3D gait analysis has yet to be evaluated in Parkinsonian patients following a MSK intervention. It is expected that the aforementioned intervention, through better rhythmicity, may improve the automatization of motor control, gait kinematics, and kinetics—supported by decreased frontal cortex hemodynamic activity—which may be linked to reduced anxiety levels.

## 1. Introduction

Parkinson’s disease (PD) is a neurodegenerative disorder with increasing rates in Western civilization. According to the World Health Organization, the prevalence of the disease has increased by 81% since 2000 [1].

Increased levels of anxiety, gait impairments, and lack of coordination are common non-motor and motor symptoms in PD, and can seriously impact patients’ overall quality of life. For instance, anxiety is a common psychiatric commonality in PD with symptoms occurring in between 20 and 52% of patients, while motor fluctuations—which are often accompanied by alterations in non-motor symptoms—can be seen in up to 75% of PD patients [2]. It has been found that fluctuations of non-motor parameters are considered risk factors for anxiety [3], and are associated with worse subjective motor symptoms, more severe gait problems, dyskinesia, and/or episodes of freezing [2,4]. However, although anxiety seems to be an important manifestation of PD, there is a lack of research regarding non pharmacological treatments [4].

As anxiety is associated with mobility difficulties in this population [2], it can be hypothesized that the lack of controlled rhythmic movement may be a factor exacerbating the condition. Gait impairment and lack of coordination are also associated with the disruption of patients’ internal rhythm, as dysfunction of basal ganglia has been linked to uncoordinated movement patterns [5,6]. Inner rhythm itself comprises the organizational characteristic of human movement reflected by its repetitive nature, and affects critically important elements of quality of life [7].

The potential mechanistic link between increased anxiety and gait-impairment severity of PD patients may be two-fold: Firstly, through increased conscious motor control. It has been previously hypothesized that decreases in automatization and rhythmicity, and their corresponding detrimental effects on gait, may be compensated for by enhanced conscious motor control. This process is mediated by increased activation of the pre-frontal cortex and, in particular, the dorsolateral pre-frontal cortex (DLPFC) [8]. Secondly, through detrimental effects of increased anxiety and rumination on executive functioning and working memory [9,10]. Based on this concept, if PD patients preferentially utilize executive motor control during the gait, the activation of these areas (i.e., DLPFC) would be enhanced, and higher anxiety levels would subsequently impair executive function, upon which gait is greatly dependent.

Humans have the tendency to synchronize their steps with the beat of the music they are listening to [11]. This phenomenon is associated with rhythm, the primal aspect of music, highlighting the close link between rhythm, movement, and dance as fundamental aspects of human existence [11]. Research in PD has revealed that rhythmic training seems to improve synchronization of neural activity in the brain, especially in the basal ganglia [12]. A systematic review evaluating the effect of rhythmic auditory stimulation on motor and non-motor parameters in PD patients revealed positive effects on gait parameters and mobility [13]. Another study revealed that rhythmic movement interventions that incorporate visual and auditory cues can improve sensorimotor integration [14]. However, rhythmics or musicokinetic education have not been examined in patients with PD. 

Rhythmics or musicokinetic education considers the human as a physical mental and spiritual entity. It is based on Francois Delsarte’s (1811–1871) and Jaque Dalcroze’s eurhythmics method (JDE), while more kinetic elements have been added throughout the years, especially for dance purposes, without neglecting the rules of music [15]. The term musicokinetic training (MSK for PD) is used herein. 

The aim of the proposed study is to examine the acute effects of a MSK program on select kinematic and kinetic parameters alongside DLPFC hemodynamics during gait initiation and steady-state walking in individuals with PD, performed in the following conditions: (a) a synchronous learning format and (b) an asynchronous remote video-based format. The program is customized for PD patients without deviating from the objectives of musicokinetic education. Primary outcomes will be the acute effects of a MSK protocol in people with PD on anxiety and locomotion. Secondary outcomes will be the effectiveness of an asynchronous remote video-based format for those patients that are not able to attend classes on site.

The novelty of the current design is the combined implementation of functional near-infrared spectroscopy (f-NIRS) in parallel with 3D gait analysis, which, until now, has yet to be evaluated in Parkinsonian patients following a MSK intervention. f-NIRS is extensively employed in chronic neurological disorders associated with aging, enabling direct measurements of the absolute concentrations of oxygenated and deoxygenated hemoglobin in the brain [16]. In relation to Parkinson’s disease, f-NIRS investigates the activity of the prefrontal cortex during tasks such as gait, postural stability, and dual-task performance, thereby determining motor vs. non-motor effects and executive dysfunction due to the disease’s pathology [16]. We shall non-invasively evaluate DLPFC hemodynamic activity in Brodmann area 46 during gait kinematics and kinetics evaluation using f-NIRS in order to investigate the cognitive involvement. Moreover, we argue that f-NIRS in conjunction with 3D gait analysis may provide valuable insights for understanding the mechanisms underlying the benefits of MSK program for PD.

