### 2.2. Inclusion and Exclusion Criteria

Participant inclusion criteria: (1) Hoehn and Yahr (H&Y) Parkinson disease scale I-III, (2) up to 75 years of age, (3) no restriction on disease duration, gender, or type of drug therapy, except for stable antiparkinsonian medication of at least 6 months, (4) data collections “on” medication, (5) no participation in any exercise program for at least 2 months, and (6) 100% attendance of the session. Exclusion criteria will include patients with dementia, cancer, cardiovascular diseases, poor visual or auditory capability and musculoskeletal problems, stable antiparkinsonian therapy, and patients with deep brain stimulation.

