### 2.6. Intervention

All intervention classes, synchronous and asynchronous remote video-based, will be held in the Biomechanics & Ergonomics Laboratory (b) at the Department of Physical Education and Sport Science, University of Thessaly, Trikala, Greece. Their structure is focusing on refining innate musicality and coordination via rhythmic movement, hearing training and improvisation.

Risk management strategy includes a qualified carer who will be present during both the synchronous and asynchronous modalities, full explanation of the experimental procedures, controlled laboratory temperatures at about 22° Celsius, as well as the continuous presence of at least two members of the research team.

The protocol has a duration of 45 min of rhythmic training and includes sections of warming up, stretching, breathing, movement combinations, a dance sequence, and recovery. Each exercise is accompanied by music that provides a clear and predictable rhythm. More specifically, the beat or rhythm of the music is used as a guide for the timing and duration of specific movements, allowing people with PD to coordinate their movements with the music. Simple values will be introduced, such as whole notes, half notes, and quarter notes, clapping and tapping, breathing, and sounds. Class will be accompanied by recorded classical piano music to meet the needs of the synchronous learning format and asynchronous remote video-based format. The intensity of the class will be moderate, at approximately 3 MET. The instructor will be an experienced dance teacher in musicokinetic education. Protocol details can be found in Table 1.

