## 3. Expected Results

The aim of the proposed study is to examine the acute effects of a MSK program on anxiety levels and select kinematic and kinetic parameters alongside DLPFC hemodynamics during gait initiation and steady-state walking in individuals with PD, performed in the following conditions: (a) synchronous learning format and (b) asynchronous remote video-based format. The program is customized for PD patients without deviating from the objectives of musicokinetic education. Primary outcomes will be the acute effects of a MSK protocol in people with PD on anxiety and locomotion. Secondary outcomes will be the effectiveness of asynchronous remote video-based format for those patients that are not able to attend classes on site. To our knowledge, this is the first time that MSK program will be introduced in PD as a form of exercise. Since motor dysfunctions are associated with anxiety [2], rhythmic-based interventions can potentially improve or even regulate it.

Anxiety may be a result of the neurochemical changes of the disease itself or a psychological reaction to the stress of the disease, and can be seen in various manifestations such as phobia, generalized anxiety disorder, or panic attacks [3,26]. The rationale behind the use of the purpose-designed MSK program for PD is its effectiveness in addressing the primordial motor expression of humans. Guidance by the rules of music, where periodicity is distinct, may eventually be beneficial in “calibrating” the brain, reducing motor difficulties, restoring movement harmony, and, thus, reducing anxiety. Moreover, we expect that the combined influence of improved rhythmicity, potentially improving the automatization of motor control, would be reflected in decreased DLPFC activation due to reduced executive load in the planned control of movements.

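### The secondary objective claims effectiveness of remote delivery for patients who cannot attend, but both formats are delivered on site, under supervision, to people who attend

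*Protocol article*

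**What the plan says.** The Introduction of the protocol article (Section 1) states the secondary objective: "Secondary outcomes will be the effectiveness of an asynchronous remote video-based format for those patients that are not able to attend classes on site". Section 3 (Expected Results) gives the secondary outcome again as the "effectiveness of asynchronous remote video-based format for those patients that are not able to attend classes on site".

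Section 2.6 fixes where and how the classes are given: "All intervention classes, synchronous and asynchronous remote video-based, will be held in the Biomechanics & Ergonomics Laboratory". As risk management it specifies "a qualified carer who will be present during both the synchronous and asynchronous modalities", together with the "continuous presence of at least two members of the research team".

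Section 2.2 lists "100% attendance of the session" among the inclusion criteria. Sections 2.4 and 2.7 have each volunteer take both formats in random order and return for a third, control occasion, with laboratory measurements before and after each.

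Section 2.9 describes the secondary comparison as one format against the other. It is judged on the measurements already listed and on how those who finish the protocol respond. That section does not mention patients who cannot attend.

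**The concern.** The stated secondary outcome names a setting (remote) and a population (patients who cannot come to classes), and the design provides for neither. The recorded-video condition is remote only in the sense that the instruction comes from a recording. The place, the carer and the attending research staff are specified alike for both formats.

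What is at stake is the conclusion that the trial will be allowed to draw. Section 3 expects the two formats to work equally well because content and teaching style are the same. If the results look similar, the present wording invites a report that remote delivery works for people who cannot attend. The data would support only a statement about recorded versus live instruction in people who came to the laboratory and were supervised there.

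**Working it through.** No arithmetic applies, because the objective carries no figure. The check is to set what the objective needs beside what the design supplies.

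| Element | What the secondary objective needs (Sections 1 and 3) | What the design supplies |
|---|---|---|
| Place of delivery | Away from the class site | The laboratory, for both formats (Section 2.6) |
| Supervision | That of remote delivery, which the article does not specify | A carer and at least two researchers, in both formats (Section 2.6) |
| Population | Patients not able to attend on site | Volunteers who meet a full-attendance criterion (Section 2.2) and come for both formats and a control occasion (Sections 2.4 and 2.7) |
| Basis of judgement | Effect of the format in that setting and population | Laboratory measurements and the response of those who complete (Section 2.9) |

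1. **Setting.** Section 2.6 covers all classes and names the recorded-video ones explicitly. No other section describes a session at home or at any other site.
2. **Population.** The eligibility list in Section 2.2 covers disease stage, age, medication, exercise history, attendance and comorbidity. Inability to attend classes is not a criterion. With two intervention occasions and one control occasion, each participant makes at least three laboratory visits.
3. **What differs between the formats.** By design it is the mode of instruction: live and synchronous in one, pre-recorded in the other. That contrast can be estimated from this cross-over.
4. **What cannot be reached.** Moving from that contrast to remote delivery for patients who cannot attend requires two further steps: from supervised laboratory to another setting, and from attenders to non-attenders. The trial collects no data on either step, and the article nowhere labels the claim as an extrapolation.

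**The case against.** The best defence is that the formal outcome section, 2.9, already defines the comparison narrowly as format against format. On that view the phrase about patients unable to attend only says for whom the video format is intended. It is also true that motion capture and embedded force platforms tie the measurements to the laboratory, that on-site delivery and supervision are openly disclosed, and that a study of one 45-minute session per format was never going to address adherence or unsupervised practice.

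Much of this stands. Section 2.9 contains no population claim, and there is good reason to test on site. The sentences in Sections 1 and 3, however, state what the secondary outcomes will be and include the target patients in that statement, without a caveat. Nor is this a matter of detail condensed for a journal: objective, venue, supervision and attendance rule are all stated, and they do not fit together.

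Three stronger readings are tempting, and the documents do not support them.

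- A reader might infer that the comparison is biased toward no difference. For the contrast actually tested, live against recorded, holding place and supervision equal removes confounding. Relative to home delivery, the documents give neither the direction nor the size of any gap.
- A reader might infer that none of the 13 participants belongs to the group unable to attend classes. Making the study visits does not show that a person could attend classes regularly, and nothing on this is recorded.
- A reader might infer that company is the same in both formats. The article does not say whether classes are individual or in groups, and a live instructor is presumably present in one format only.

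**Conclusion.** The point holds as a mismatch between the stated secondary objective and the design. The trial can answer whether a pre-recorded video-led session and a live instructor-led session differ in acute effect, both under on-site supervision, in people who attend. It cannot show effectiveness of remote delivery in patients who cannot attend.

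The consequence is confined to the secondary claim. The primary outcomes, randomisation, sample size and analysis are not affected. No numerical size can be given, because the trial contains no off-site session from which a setting effect could be estimated.

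The conclusion rests on reading 'remote' in Sections 1 and 3 together with the patients named there. If 'remote' is meant only as a synonym for recorded instruction, the label is loose rather than wrong, but the reference to patients unable to attend is still unsupported.

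**What to change.** - **Sections 1 and 3:** restate the secondary objective and the corresponding conclusion as *a pre-recorded video-led session compared with a live instructor-led session, both under on-site supervision*. Remove the claim about patients unable to attend, and name home delivery as a question for a later study.
- **Section 2.9:** only qualify the label 'remote' so that it matches, for example by stating that the recorded session is delivered in the laboratory. There is no population claim here to remove.

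This changes wording only; procedures, visits and measurements stay as they are. The cost is a narrower secondary claim.

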## 2. Materials and Methods

### 2.1. Participants

Patients from central Greece diagnosed with PD will be asked to volunteer. PD diagnosis will be connected to certified neurologists, according to Movement Disorders Society (MDS) clinical diagnostic criteria. The campaign to attract volunteers will be organized by the Department of Physical Education and Sport Science, University of Thessaly, Greece, the local Medical Association, local authorities, and social media.

### 2.2. Inclusion and Exclusion Criteria

Participant inclusion criteria: (1) Hoehn and Yahr (H&Y) Parkinson disease scale I-III, (2) up to 75 years of age, (3) no restriction on disease duration, gender, or type of drug therapy, except for stable antiparkinsonian medication of at least 6 months, (4) data collections “on” medication, (5) no participation in any exercise program for at least 2 months, and (6) 100% attendance of the session. Exclusion criteria will include patients with dementia, cancer, cardiovascular diseases, poor visual or auditory capability and musculoskeletal problems, stable antiparkinsonian therapy, and patients with deep brain stimulation.

### 2.3. Sample Size Calculation

The total sample size was estimated through an a priori power analysis, using the G power V 3.1.9.7 software (Heinrich-Heine-Universität, Düsseldorf, Germany). The following input parameters were applied using a repeated-measure ANOVA design: effect size f = 0.33, α = 0.05, power = 0.80, and correlation between repeated measures r = 0.50. The a priori power calculation revealed that the initial sample size required is 11. By considering a 10% dropout rate, 13 individuals with Parkinson’s disease will be recruited to voluntarily participate in this study.

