### 2.7. Outcome Measures

Volunteers will attend both conditions (synchronous and asynchronous remote video-based) in a randomized order, separated by a washing-out period of at least a week. Kinematic, DLPFC hemodynamic activity and levels of anxiety data will be collected before (base-line data) and after the two interventions, while, on a third occasion, control data will be collected at the same time points but without any intervention.

Two experienced evaluators blinded to the group allocation will collect data. Baseline data collection will include: (1) Anthropometric characteristics (sex, age, body mass index), H&Y scale; (2) Anxiety Hamilton Rating Scale (Hamilton 1960); (3) Gait analysis using a 10-camera 3D motion analysis system (Vicon T-series, Oxford, UK) and two force platforms (Bertec 4060–10, OH) embedded in the laboratory floor; (4) Frontal cortex hemodynamic responses using f-NIRS (Portalite by Artinis NL); and (5) Unified Parkinson’s Disease Assessment Scale-III (UPDRS-III). Post intervention measurements will include: (1) Anxiety Hamilton Rating Scale (Hamilton 1960); (2) Gait analysis using a 10-camera 3D motion analysis system (Vicon T-series, Oxford, UK) and two force platforms (Bertec 4060–10, OH) embedded in the laboratory floor; (3) Frontal cortex hemodynamic responses using f-NIRS (Portalite by Artinis NL); and (4) Unified Parkinson’s Disease Assessment Scale-III (UPDRS-III).

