### 2.10. Statistical Analyses

The normal distribution of the dataset will be assessed using the Shapiro–Wilk test. Analyses of variance (ANOVAs) with repeated measures will be used to analyze kinematic and kinetic parameters and pre-frontal cortex hemodynamic responses during gait initiation and during the steady state between the two interventions and time points. Significant interactions and main effects will be further examined using Bonferroni post hoc analysis. The significance level will be set at *p* < 0.05.

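### The 11 patients for 80% power correspond to a six-mean omnibus test, so 80% power is not shown for the effect of MSK against control

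*Protocol article*

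**What the plan says.** Section 2.3 introduces the calculation with "The following input parameters were applied using a repeated-measure ANOVA design", lists "effect size f = 0.33, α = 0.05, power = 0.80, and correlation between repeated measures r = 0.50", and reports that "The a priori power calculation revealed that the initial sample size required is 11". It then adds: "By considering a 10% dropout rate, 13 individuals with Parkinson’s disease will be recruited". It does not give the number of groups or measurements, the effect or outcome to which f = 0.33 belongs, or the sphericity correction.

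The design has three occasions. Each patient attends both formats and, under section 2.7, "on a third occasion, control data will be collected at the same time points but without any intervention". With a measurement before and after on each occasion, that makes six means.

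The analysis in section 2.10 compares outcomes "between the two interventions and time points", which is four means, and control is not named. It adds that "Significant interactions and main effects will be further examined using Bonferroni post hoc analysis".

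The Introduction states the main question: "Primary outcomes will be the acute effects of a MSK protocol in people with PD on anxiety and locomotion". The remote format is a secondary matter there.

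**The concern.** Three parts of the plan should concern the same test: the sample-size calculation, the planned ANOVA and the primary question. Here they appear to concern three different ones. The calculation fits six means, the ANOVA has four, and the primary question in a trial with a control condition is one contrast: does the pre-post change after MSK exceed the change without it?

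The 80% figure is the only justification given for 13 patients. If it belongs to a test nobody will interpret, readers will credit the controlled comparison with a sensitivity that has not been shown. A null result on that comparison could then be over-read.

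**Working it through.** **Inputs.** f = 0.33, α = 0.05, r = 0.50, N = 11 and 13 (section 2.3). The layouts come from sections 2.7 and 2.10. Assumed because not stated: one group, sphericity (ε = 1), the same r between any two measurements, and no period or carry-over effect.

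**Step 1: reproduce the stated 11.** For the within-factors test with m measurements:

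λ = f²·N·m/(1 − r), df1 = m − 1, df2 = (N − 1)(m − 1), power from the noncentral F.

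For m = 6 and N = 11: λ = 0.1089 × 11 × 6/0.5 = 14.37 on 5 and 50 df, power 0.802. For N = 10: λ = 13.07, power 0.751. So N = 11 reproduces. Dropout: 11/0.9 = 12.2, so 13, which is correct.

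| Measurements | N for 0.80 | Power at 11 | Power at 13 |
|---|---|---|---|
| 2 | 21 | 0.507 | 0.590 |
| 3 | 17 | 0.597 | 0.687 |
| 4 | 14 | 0.679 | 0.768 |
| 6 | 11 | 0.802 | 0.879 |

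Seven measurements would also give 11, but the design has no such layout. The two-measurement row is any single two-level contrast with f = 0.33, which is a difference of 0.66 SD.

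**Step 2: what f = 0.33 over six means implies.** Suppose both post-MSK means shift by d and the other four do not. The SD of the six means is d·√(1/3 × 2/3) = 0.4714d, so d = 0.33/0.4714 = 0.70 SD.

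**Step 3: MSK change minus control change.** With r = 0.50 throughout, each pre-post change has variance 2(1 − 0.5) = 1, and changes on different occasions are uncorrelated.
- Both formats averaged, minus control: variance 1/4 + 1/4 + 1 = 1.5, SD 1.225, standardised effect 0.70/1.225 = 0.572. Using the contrast's own error (N − 1 df), power is 0.403 at 11 and 0.474 at 13. Using the pooled interaction error (2(N − 1) df), it is 0.438 and 0.507. With the contrast's own error, 0.80 needs 27 completers.
- One format minus control: variance 2, SD 1.414, standardised effect 0.495. Power is 0.32 at 11 and 0.38 at 13.

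**Step 4: pre-post main effect over the two formats, without control.**
- With f = 0.33 defined over the four means: λ = 0.1089 × 11 × 4/0.5 = 9.58 on 1 and 10 df, power 0.796. At 13, λ = 11.33, power 0.870.
- Under the 0.70 SD shift: the averaged change has variance 0.5, standardised effect 0.70/0.707 = 0.990. Power is 0.84 at 11 and 0.91 at 13.

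**Step 5: baseline-adjusted contrast.** With a common r, the baseline contrast is uncorrelated with the post contrast, so adjustment reduces to comparing post values: variance 1.5 × (1 − 0.5) = 0.75, SD 0.866, standardised effect 0.70/0.866 = 0.808. Power is 0.68 (10 df) to 0.72 (20 df) at 11, and 0.76 (12 df) to 0.80 (24 df) at 13.

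**The case against.** The strongest reply is that nothing has been miscalculated. Six measurements is the trial's true layout, 11 reproduces, and so does 13. That stands.

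A reader might infer from the table that the section 2.10 analysis needs 14 patients. The documents do not support this. The four-mean row is itself an omnibus test, on 3 df, whereas a 2 × 2 repeated-measures ANOVA tests three 1-df effects. With f = 0.33 defined over the four means, any of these has power 0.796 at 11 and 0.87 at 13. It is therefore also wrong to say that nothing in the planned ANOVA reaches 80%. But these effects do not answer the controlled question. The time effect makes no use of the control occasion. For the format-by-time interaction, f = 0.33 means changes of +0.66 and −0.66 SD around their mean, a difference of 1.32 SD between formats that section 3 expects to be equally effective.

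It can also be said that the low figures depend on a meaning of f that section 2.3 does not give. That is fair. If f = 0.33 belonged to the 2-df occasion-by-time interaction over six means, power would be 0.89 at 11 and 0.94 at 13. With both formats changing by c and control flat, λ per patient is (2/3)c² = 0.1089 × 6/0.5 = 1.307, so c = 1.40 SD. That is twice the 0.70 SD shift. The text does not exclude it, but nothing in the text supports it either.

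Finally, a condensed article may leave settings to a fuller document. That excuses the missing software options. It does not resolve the mismatch between the calculation and the analysis that the article does print.

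**Conclusion.** The point holds as a mismatch, not as an arithmetic error. Among the layouts the design allows, the published inputs give 11 only for a 5-df test over six means. That test can reject because occasions or baselines differ. It is neither the ANOVA in section 2.10 nor a test of MSK against control, so the stated 80% is not shown for the controlled primary question.

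Under the 0.70 SD shift implied by f = 0.33, power for the averaged MSK-minus-control change is about 0.40–0.44 at 11 completers and 0.47–0.51 at 13. It is about 0.32 and 0.38 for one format against control. These figures assume that both formats shift equally, that control is flat, and that sphericity and a common r of 0.50 hold. If sphericity fails, even the omnibus figure drops: at ε = 0.75 it needs 14, with power 0.705 at 11. Only the uncontrolled pre-post effect over both formats reaches about 0.80 or more.

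**What to change.** - In section 2.3, state the number of measurements entered, the sphericity setting, and the effect and outcome to which f = 0.33 refers.
- In section 2.10, include the control occasion so that the analysis matches the three-occasion design, and name the MSK-versus-control contrast.
- Replace the general 80% statement with the power, or the detectable difference, for that contrast at 11 and 13 completers. If f is confirmed as the spread over six means, a 0.70 SD effect gives about 0.40–0.44 and 0.47–0.51 analysed as change, and about 0.68–0.72 and 0.76–0.80 with baseline adjustment. The ranges reflect the choice of error df.
- Describe comparisons between the two formats as estimation, with confidence intervals.

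This is rewording plus one added condition in the analysis, using data already planned. No extra patients or visits are needed. The cost is a less favourable stated power.
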